## Methods

### Setting

WACHS delivers healthcare services to over 550,000 people across 2.5 million square kilometres.^24,25^ There are 103 WACHS-run health facilities, including six large regional hospitals, 15 medium-sized district hospitals, 48 small hospitals, and 34 health centres and nursing posts across seven geographically dispersed regions. There are additional non-WACHS health facilities and Aboriginal Medical Services that are outside the scope of this research.

The majority of smaller health facilities are operated by generalist nurses, with medical cover provided by a local general practitioner. Each region is unique in its population, geography, health needs, and service availability, and all classified as rural and remote according to the Australian Statistical Geography Standard (ASGS) Remoteness Structure.^
1
^ The ASGS is based on the road distances people have to travel for services.^
1
^
Figure 1 shows the seven WACHS regions, overlayed with the measure of remoteness.

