RE-AIM dimension	Expanded RE-AIM & IOF definition	Data measure	Data collection
Reach	Number of individuals exposed to the intervention	Number of CC patient contacts (by site, health facility type, region) for each command centre service	Service data
	Proportion of intended audience who participate in the intervention	Proportion of CC patient contacts compared to total health facility presentations	Service data
	Representativeness of individuals relative to the intended population	CC Patient contact characteristics (age group, sex, postcode, Aboriginal and/or Torres Strait Islander status, priority category, diagnosis)	Service data
Effectiveness	The degree to which the intervention is producing its intended effects while assessing potential unintended consequences and changes in quality of life	Degree to which staff agree that the intended objectives of the CC are being met	Survey Interviews
Adoption	Number of settings that participate in or are exposed to the intervention. (Organisational level)	Number of sites where CC services and infrastructure have been implemented (by health facility type and region) for each CC service	Service data
	Proportion of the intended settings who deliver or are exposed to the public health intervention. (Organisational level)	Number of sites actively using CC services compared to where services and infrastructure have been implemented by not being actively used. Determined by patient volume.	Service data
	Representativeness of settings relative to the intended population who participate in or are exposed to the public health intervention. (Provider level)	Number and characteristics of front-line providers using the CC (by site, health facility type, region) for each service	Survey
	Antecedent assessment of service recipient perception (Provider level)	Front-line provider attitudes and perceptions of CC services Normalisation MeAsure Development (NoMAD) questionnaire^ 39 ^	Interviews Survey
Implementation	Consistency of delivery as intended and in the time required across staff and organisations	Fidelity: Rollout of services according to implementation plan	Service data Interviews Project initiation documents Operational guidelines
	Adaptation Assessing indicators of adaptation prior to, during, and following implementation of the intervention	Local adaptations Cultural adaptations	Survey Interviews Project initiation documents Operational guidelines

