#### Phase 1: command centre service data analyses

Data from each of the CC services will be collated from the date of implementation, or when useful data collection commenced, to the date of data extraction. These vary based on the service, with dates to be outlined on analyses.

Variables to be collected and analysed for each service are framed around the evaluation of implementation status and implementation outcomes, integral and proceeding to successful service and clinical outcomes.^
35
^ Service data will be collected for all ‘service contacts’ across the 103 WACHS-run health facilities, which were referred to the CC. No individual staff data are collected in the service data, therefore ‘Episode’ volume will be used to demonstrate the reach (patient level) and adoption (organisational level), as outlined in Table 2.

CC service data will be analysed via descriptive statistics including measures of frequency, percentages, central tendency, and variation. The analyses will describe each CC service, by site, by region, and by health facility type. Prior to analyses, the data will be transformed into a suitable format across the services to enable cross-tabulation across variables. The data will also be checked for missing or not applicable data or the presence of any anomalies. Inferential statistics will be used to test for analysis of variance between patient contacts (dependent variable) and the region, health establishment type, and site (Independent variables), per service.^
41
^

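### Phase 1 compares use by region, facility type and site without a stated adjustment for case mix or setting, so crude differences may partly reflect need rather than uptake

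*Protocol article*

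**What the plan says.** The Phase 1 section fixes both the description and the test. On description: "The analyses will describe each CC service, by site, by region, and by health facility type". On inference, the plan is to "test for analysis of variance between patient contacts (dependent variable) and the region, health establishment type, and site (Independent variables), per service". Because the service data hold nothing on individual staff, episode "volume will be used to demonstrate the reach (patient level) and adoption (organisational level".

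The Setting section describes places that are not alike: "Each region is unique in its population, geography, health needs, and service availability". It adds that "The majority of smaller health facilities are operated by generalist nurses, with medical cover provided by a local general practitioner". Remoteness appears there as part of a map: "Figure 1 shows the seven WACHS regions, overlayed with the measure of remoteness". It is not named as an analysis variable.

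Table 2 bears on the point in three places:

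- Under Reach, it lists CC contacts as a proportion of all presentations at the facility.
- Also under Reach, it lists "CC Patient contact characteristics (age group, sex, postcode, Aboriginal and/or Torres Strait Islander status, priority category, diagnosis", as a description of the patients who were referred.
- Under Adoption, the row defined as representativeness of settings, labelled provider level, is filled with "Number and characteristics of front-line providers using the CC (by site, health facility type, region) for each service", taken from the survey.

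The Background section on rural provider-to-provider telehealth lists the handling of selection bias and confounding by statistical means among the recommendations that this research intends to meet.

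**The concern.** The explanatory variables in the Phase 1 test are three administrative labels. The protocol itself says that need and service availability vary across one of them, region. It ties nurse-run care with general practitioner cover to smaller facilities, so medical cover varies with another, facility type. A region may show high volume because more of its patients are acutely ill, or because no doctor is on site, and not because its staff are readier to call. The planned comparison cannot separate these.

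Dividing by total presentations removes differences in facility size. It does not remove differences in the mix of patients presenting.

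Phase 1 also supplies the pattern that the rest of the study works on. Phase 3 uses survey and interview data to illustrate and explain the service data, and recommendations follow. If part of a regional gap is case mix, the later phases may look for attitudes and barriers behind a difference that has little to do with them. The stated intention to deal with confounding statistically is not carried through: Phase 1 names no such method, and the survey analysis is descriptive.

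**Working it through.** **The plan's own figures.** Phase 1 states no sample size, effect or power, so there is nothing of its own to reproduce. The only computed figure in the document is the survey size, and it does reproduce: 1.96² × 0.25 / 0.05² = 384.1; 384.1 / (1 + 383.1/6000) = 361.1, rounded up to 362. It plays no part in this point.

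**Does a proportion of presentations remove case mix?** Let *s* be the share of high-priority presentations in a region, *h* the share of those referred, and *l* the share of other presentations referred. The crude referral proportion is

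p = s·h + (1 − s)·l

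Set *h* = 0.30 and *l* = 0.05 at every site, so that behaviour is identical. These values and the shares below are assumptions; the documents give none.

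- s = 0.40: 0.40 × 0.30 + 0.60 × 0.05 = 0.150
- s = 0.15: 0.15 × 0.30 + 0.85 × 0.05 = 0.0875; ratio 0.150 / 0.0875 = 1.71
- s = 0.30: 0.30 × 0.30 + 0.70 × 0.05 = 0.125
- s = 0.20: 0.20 × 0.30 + 0.80 × 0.05 = 0.100; ratio 0.125 / 0.100 = 1.25

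The result depends on the inputs. Four pairs of (*h*, *l*) were tried: 30%/5%, 20%/5%, 10%/5% and 50%/2%. Each was combined with shares of 40% v 10%, 30% v 20% and 25% v 15%. The extremes were:

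- *h* = 0.10, *l* = 0.05, shares 30% v 20%: 0.065 / 0.060 = 1.08
- *h* = 0.50, *l* = 0.02, shares 40% v 10%: 0.212 / 0.068 = 3.12

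**Would the planned kind of test pick this up as a regional difference?** A simulation used 87 enabled sites spread over 7 regions, a mean high-need share of 25%, a within-region SD of 5 points, log-normal presentation volumes (log mean 7, log SD 0.5) and referral of 30% and 5%. One-way analysis of variance across regions was run at the 5% level, with 2,000 runs per row. Apart from the counts of sites and regions, every input is assumed. The table gives the percentage of runs in which the region test rejected, although uptake given need was the same everywhere.

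| Between-region SD of need share | Raw contacts | Proportion of presentations | Standardised for need |
|---|---|---|---|
| 0 | 4.5 | 4.95 | 4.15 |
| 0.05 | 18.2 | 95.3 | 5.3 |
| 0.10 | 61.65 | 99.8 | 5.15 |
| 0.15 | 85.15 | 100 | 7.65 |

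Using the proportion makes the case-mix effect easier to detect, because it strips out the noise from facility volume and leaves the difference in mix. Standardising for need brings rejection back to about the nominal level, slightly above it at the widest spread.

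**The case against.** The strongest reply is that Phase 1 answers a descriptive question. Objective 1 asks what the differences in reach and adoption are; explaining them is Objective 2, which the protocol assigns to Phase 2, with integration in Phase 3. That is how an explanatory sequential design works. This stands, and it is why the crude results should stay. It does not settle the matter, because the survey and interviews can suggest that acuity or medical cover matters but cannot say how much of a regional gap these account for.

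The plan is also not blind to the issue. It has the presentations denominator, the contact characteristics, facility type as a coarse proxy for medical cover, cross-tabulation across variables, and confounding named as a limitation with ROBINS-I as the tool. So a reader who inferred that Phase 1 takes no account of setting or case mix would go too far. But the contact characteristics are listed for referred patients only and cannot by themselves adjust a referral rate, and ROBINS-I appraises bias without adjusting for it.

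Three further inferences are not supported:

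- That Phase 1 selects low-use sites for later study. The survey targets the whole workforce of about 6000, interviews draw on survey volunteers, and the forum uses purposive and convenience sampling.
- That Figure 1 gives every facility a remoteness class. The text describes remoteness laid over regions.
- That volume differences will certainly be misread as differences in willingness to use the service. No section commits to that reading.

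Remoteness and medical cover may themselves be reasons for differential use, and adjusting them away could hide what Objective 2 seeks. That is right, and it shapes the fix. Lastly, a covariate list could sit in a fuller plan that is not shown; but this article does state the outcome and the factors of the test.

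**Conclusion.** The point holds in a limited form. As stated, the Phase 1 comparison has no adjustment or stratification for case mix or setting, although the protocol says that need and service availability differ by region and that it intends to address confounding statistically. Crude differences, including those in the proportion of presentations, may partly reflect who presents and what cover exists locally.

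The size in this trial is unknown. On assumed inputs the spurious ratio between two regions ran from 1.08 to 3.12. That shows the effect can be anywhere from negligible to large; it does not estimate it. The descriptive answer to Objective 1 is not invalid. What is at risk is the interpretation carried into Phases 2 and 3. This is an inexpensive improvement to the plan and not a flaw that undermines the study.

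**What to change.** 1. Keep the crude results by site, region and facility type as the descriptive answer to Objective 1.
2. Beside them, for facilities where the service is enabled (87 of 103 for the suite), report referral rates from a count or rate model with total presentations as the offset, region and facility type as factors, and site as a random effect. Site should not be a fixed factor: anything constant within a facility, such as remoteness or medical cover, would then be fully aliased with it.
3. Adjust or stratify for priority category, age group, and Aboriginal and/or Torres Strait Islander status, where these can be obtained for all presentations and not only for CC contacts. If they cannot, state that regional differences cannot be read as differences in uptake.
4. Show results with and without each facility's ASGS remoteness class, assigned from its location, and its medical-cover model, since these may be explanations and not nuisances.
5. Carry the crude and adjusted patterns together into the Phase 3 integration.
6. In Table 2, add to the Adoption row on representativeness of settings a comparison of using, non-using and non-enabled facilities by type, region and remoteness.

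The cost is modest extra analysis, a one-off tabulation of remoteness and medical cover by facility, and a request for presentation counts by case-mix category. The protocol does not say whether those counts are available, which is why step 3 has a fallback.

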### Model of service

The WACHS CC began operations in 2012 as the Emergency Telehealth Service (ETS), a virtual health solution to support diagnosing, treating, and managing patients in local regions.^
26
^ The ‘Command Centre’ was officially launched in 2019 from recommendations of the Department of Health, Western Australia's Sustainable Health Review.^
27
^ A suite of services have since been implemented, beginning with the Inpatient Telehealth Service, and Mental Health Emergency Telehealth Service, and more recently, the Midwifery and Obstetrics Emergency Telehealth Service,^
28
^ and the Palliative Care Afterhours Telehealth Service.^29,30^ While these services differ in their functionality and purpose, they all deliver provider-to-provider specialist and clinical advice via virtual means, supporting the front-line clinicians caring for patients in rural and remote areas. The CC's Clinical services aims are as follows:
Facilitate appropriate decision making in the treatment and care of country patients.Support our place-based workforce by providing guidance, advice, and access to specialist knowledge to help provide the best care possible for rural and remote patients.Build a collaborative, integrated workforce, blending place-, and remote-based clinicians to deliver care to the highest possible quality and safety standard and in the most culturally appropriate way.Unlike other virtual or telehealth care, which is often between the patient and provider, these services are usually between the rural and remote front-line provider, with the patient present, and the specialist provider. The suite of CC services is enabled in 87 of the 103 health facilities.

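### The Phase 1 test compares raw contact counts across region, facility type and site without a denominator, so it cannot separate uptake from facility size and time enabled

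*Protocol article*

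**What the plan says.** Phase 1 (Command Centre service data analyses) is mainly descriptive and adds one inferential step, carried out per service: "Inferential statistics will be used to test for analysis of variance between patient contacts (dependent variable) and the region, health establishment type, and site". The same section takes episode volume as the indicator of both reach and adoption. No denominator, offset or observation time is attached to the tested variable.

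Table 2 lists two different Reach measures from the service data. One is a count: "Number of CC patient contacts (by site, health facility type, region) for each command centre service". The other is relative: "Proportion of CC patient contacts compared to total health facility presentations". The inferential sentence picks up the first and not the second. For Adoption, Table 2 divides implemented sites into those using the services and those not using them, and the entry ends "actively used. Determined by patient volume".

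On the sites themselves, the Setting section says: "There are 103 WACHS-run health facilities, including six large regional hospitals, 15 medium-sized district hospitals, 48 small hospitals, and 34 health centres and nursing posts". They are spread over seven regions. Under Model of service: "The suite of CC services is enabled in 87 of the 103 health facilities". The Design section and the third limitation in the Discussion say that the services have run for differing lengths of time and began at different times and locations.

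**The concern.** Table 1 asks how reach and adoption differ across regions, sites and facility types, and the Phase 1 test is the only inferential analysis that the article names. The survey is to be analysed descriptively and the interviews thematically. If the outcome is a raw count, a large regional hospital will show more contacts than a nursing post at identical uptake, simply because more patients come through the door. A small site with high uptake can look like a low user. A site enabled earlier accumulates more contacts than one enabled later.

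The design is sequential: Phase 2 sets out to explain the differential use that Phase 1 describes, and Phase 3 builds recommendations on both. A size artefact reported as a difference in adoption would carry through. It would also sit badly with the Background, which lists statistical control of confounding among the recommendations that the research intends to cover.

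The second problem is structural. Site is not a third factor alongside region and type, because it is nested in both.

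**Working it through.** **Inputs from the article.** Facilities by type: 6, 15, 48 and 34, and 6 + 15 + 48 + 34 = 103, which reproduces the stated total. Regions: 7. Facilities with the suite enabled: 87, so 103 − 87 = 16 without. No significance level, effect size or presentation volume is given for the Phase 1 test.

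**Step 1: degrees of freedom (no assumption beyond each site lying in one region and one type).**
- Region and type together: 1 + (7 − 1) + (4 − 1) = 10 parameters.
- Site alone: 103 parameters.
- Site, region and type together: the design matrix still has rank 103. Region and type therefore have 103 − 103 = 0 df beyond site.
- One total per site: 103 observations − 103 = 0 residual df, so a site effect cannot be tested at all.
- Twelve periods per site, as an illustration: 103 × 12 = 1,236 observations and 1,236 − 103 = 1,133 residual df. Region and type still have 0 df after site.
- Region and type only, with site as the unit: 103 − 10 = 93 error df. On the 87 enabled sites it would be 87 − 10 = 77, provided every region and type is still represented.

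**Step 2: counts against rates when uptake is equal (simulation, test of facility type at 5%).** The 6/15/48/34 site mix was kept and mean presentations per type were assumed. In one set of 1,000 runs per row, mean uptake was 5% in every type, both uptake and presentations varied between sites, and type was tested adjusted for region:

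| Assumed mean presentations by type | Largest / smallest | Counts reject | Proportions reject |
|---|---|---|---|
| 20,000 / 8,000 / 2,500 / 800 | 25 | 100% | 3.8% |
| 4,000 / 3,000 / 2,000 / 1,500 | 2.7 | 86% | 4.7% |
| 2,400 / 2,200 / 2,000 / 1,800 | 1.3 | 14.4% | 5.0% |
| Equal sizes | 1 | 5.7% | 5.1% |

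A separate set of runs compared counts with log rates. Counts rejected in 100%, 99% and 24% of runs at size ratios of about 37, 2.7 and 1.3; log rates rejected in 4% to 5%. The two sets differ where size differences are small, because the rejection rate there depends on the assumed spread between sites. The direction is the same in both.

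**Step 3: can a real difference be hidden?** Contacts = presentations × uptake. With assumed presentations of 30,000 / 10,000 / 2,500 / 800 and uptake of 1% / 3% / 10% / 15%, contacts are 300 / 300 / 250 / 120. The counts run opposite to uptake. In simulation, a 25-fold uptake difference set up to be offset by size was detected in 21% of runs with counts and 100% with proportions. Both cases were constructed to show what is possible; they do not describe this service.

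**The case against.** The best defence is that the denominator is already in the plan. Table 2 includes the proportion of presentations, Table 1 asks for it, and Phase 1 will report percentages by site, region and facility type. The number of people reached is also a Reach measure in its own right. This stands in part. A reader might infer that Phase 1 cannot show differential use at all, and the document does not support that: the proportion can show it descriptively. The fault lies in the test, which is tied to the count.

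Second, the sentence lists three independent variables but does not say that they enter one model. This also stands. With separate one-way tests, region and type are estimable. The site test on single totals still has no residual df, and size remains mixed with uptake in the type comparison.

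Third, a reader might infer that region effects would be declared far too often. That holds only if repeated periods per site are analysed as independent observations, which the article does not say. With one total per site and sites allocated to regions at random, the region test on counts rejected in about 4% to 5% of runs. If regions differ in facility mix, size confounding returns there too, but that is the denominator point again.

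Fourth, a reader might infer that the 16 facilities without the suite would enter as structural zeros. The article does not say so. It only leaves their place in the test unstated.

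Finally, Table 2 gives no threshold for active use, and a near-zero cut-off on volume would do little harm. A higher one would misclassify small sites.

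Model family and random terms may be left to an analysis plan. The outcome and the factors, however, are fixed in the article.

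**Conclusion.** Wrong as written. The inferential test is fixed on a quantity that mixes uptake with facility size and time enabled, while the relative measure that the question needs is already in Table 2.

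The nesting result is exact but conditional. If region, type and site are all fixed factors in one model, region and type have 0 df beyond site. A site test on single totals has no residual df on any reading.

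The size of the bias rests on assumed presentation volumes, because the documents give none by facility. Over assumed size ratios of 1.3 to 37, equal uptake was declared unequal across types in 24% to 100% of runs in one set of assumptions. The other set gave 14% to 100% over ratios of 1.3 to 25. The excess disappears when types are equal in average size, which is hard to reconcile with the type labels in the Setting section: "six large regional hospitals, 15 medium-sized district hospitals, 48 small hospitals, and 34 health centres and nursing posts". The effect of time enabled was not quantified, since site-level start dates are not given.

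**What to change.** Change the inferential sentence in Phase 1, per service, as follows:
- **Outcome.** Test contacts relative to total facility presentations, either as a proportion or as counts with log presentations as offset, allowing for overdispersion. Use only the period in which that service was enabled at each site, and only enabled sites. State how the remaining facilities are handled.
- **Structure.** Test region and facility type with site as the unit of analysis, or with site as a random effect if repeated periods are used. Report site differences descriptively or as random-effect estimates, not as a fixed factor beside region and type.
- **Denominator by service.** Presentations may not be the natural denominator for the inpatient and palliative care services. Name the activity measure used for each.
- **Active use in Table 2.** Base it on the same rate rather than on volume alone.

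Contact counts can stay as a descriptive Reach measure. A simple rate analysis is enough, and an elaborate model is not required. The cost is a change of wording and modest extra analysis. Total presentations are already needed for Table 2. Enablement dates by site and service, and any service-specific denominators, would have to be obtained if they are not already in the extract.
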